## **2. Research Purposes**

To evaluate safety and immunogenicity of a heterologous prime-boost immunization of Inactivated SARS-CoV-2 vaccine (Vero cells) and Recombinant COVID-19 vaccine (Ad5 Vector) in healthy adults aged 18-59 years.

### **3. Trial Design**

This study is a single-center, randomized, observer blind, parallel - controlled heterologous prime-boost immunization clinical trial. 300 healthy subjects aged 18-59 years will be recruited in this study. Of them, 200 subjects who have been vaccinated with two doses of inactive SARS-CoV-2 vaccine will be recruited and randomized at a 1:1 ratio to receive a booster dose of inactivated SARS-CoV-2 vaccine or recombinant SARS-CoV-2 Ad5 vectored vaccine at an interval of 3~6 months. Other 100 subjects who have been vaccinated with one dose of inactivated SARS-CoV-2 vaccine will be recruited and randomized at a 1:1 ratio to receive a second dose of inactivated SARS-CoV-2 vaccine or recombinant SARS-CoV-2 Ad5 vectored vaccine at an interval of 1~3 months.

#### **3.1 Study Endpoints**

##### **3.1.1 Primary endpoints**

- The incidence of adverse reactions in each group within 28 days after the boost vaccination;
- Neutralising antibodies to live SARS-CoV-2 (GMT) at after the boost vaccination 14 days.

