###### **3.1.2.2 Humoral immunogenicity endpoints**

- GMT of anti-SARS-CoV-2 S and N protein specific antibody (ELISA) at Day14, Day28 and Month 6 after the boost vaccination in each group;
- GMT of neutralising antibodies to live SARS-CoV-2 at Day28 and Month 6 after the boost vaccination in each group;
- The Geometric Mean of the Fold Increase (GMFI) of antibody level of

anti-SARS-CoV-2 S and N protein specific antibody (ELISA) at Day14, Day28 and Month 6 compare with Day0 after the boost vaccination in each group;

- The Geometric Mean of the Fold Increase (GMFI) of neutralising antibodies to live SARS-CoV-2 at Day14, Day28 and Month 6 compare with Day0 after the boost vaccination in each group;
- Proportion of the participants with at least a four-fold increase of the binding antibodies against SARS-CoV-2 S and N protein at Day 14, Day 28 and Month 6 after the boost vaccination ( $\geq 4$  times increased);
- Proportion of the participants with at least a four-fold increase of neutralizing antibodies against live SARS-CoV-2 virus, as compared to baseline, at Day 14, Day 28 and Month 6 after the boost vaccination ( $\geq 4$  times increased);

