## **3.2 Sample size**

(1) Hypothesis 1: GMT of Group A is not inferior to that in the group B at Day28 after the boost vaccination.

(2) Hypothesis 2: GMT of Group A is superior to that in the group B at Day28 after the boost vaccination.

Three to six months after two doses of inactivated vaccine, the baseline GMT level before the booster is expected to be about 1:40 ( $\log_{10}X=1.6$ ), and 1:80 ( $\log_{10}X=1.9$ ) after one dose of inactivated vaccine. After receiving one dose of the

recombinant COVID-19 vaccine (Ad5 vector) as booster, the GMT is estimated to reach 1:160 ( $\log_{10}X=2.2$ ). The standard deviation is about 4 ( $\log_{10}X=0.6$ ), the sample size is calculated:

At one-sided 2.5% significance level, and the ratio of group A and group B is 1:1. To ensure at least an 90% study power, a sample size of 86 per group could show that the GMT level of group A after immunization is better than that of group B. Therefore, in order to meet both assumptions and considering a drop off of 10%, the sample size of about 100 people per group. Considering the difficulty of recruiting, Group C and Group D will have 50 persons in each to explore for exploratory purpose. The total sample size is about 300.

Table 1. Sample size of each study group

| group   | sample size | Prime immunization                    | Boost immunization                                 | Immunization procedure                                                                                              |
|---------|-------------|---------------------------------------|----------------------------------------------------|---------------------------------------------------------------------------------------------------------------------|
| Group A | 100         | Inactivated COVID-19 vaccine (2 dose) | Recombinant COVID-19 vaccine (Ad5 vector) (1 dose) | Three to six months after the second vaccination of inactivated vaccine, boost immunization will be administrated.  |
| Group B | 100         |                                       | Inactivated COVID-19 vaccine (1 dose)              |                                                                                                                     |
| Group C | 50          | Inactivated COVID-19 vaccine (1 dose) | Recombinant COVID-19 vaccine (Ad5 vector) (1 dose) | One to two months after the first vaccination of inactivated vaccine, the boost immunization will be administrated. |

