| Group D | 50          |                                       | Inactivated COVID-19 vaccine (1 dose)              |                                                                                                                     |
|         | 300         |                                       |                                                    |                                                                                                                     |

\*If Hypothesis 1 is valid, further statistical inference is made for Hypothesis 2. The GMT comparison of group C and group D after immunization is taken as the preliminary exploration, and no statistical inference is made for the sample size estimation. Considering the difficulty of recruiting people of groups C and D, the sample size is set to half of groups A and B.

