## 3.3 Sample Size

(1) Hypothesis 1: GMT of Group A is not inferior to that in the group B at Day 28 after the boost vaccination.

(2) Hypothesis 2: GMT of Group A is superior to that in the group B at Day 28 after the boost vaccination.

Three to six months after two doses of inactivated vaccine, the baseline GMT level

before the booster is expected to be about 1:40 ( $\log_{10}X=1.6$ ), and 1:80 ( $\log_{10}X=1.9$ ) after one dose of inactivated vaccine. After receiving one dose of the recombinant COVID-19 vaccine (Ad5 vector) as booster, the GMT is estimated to reach 1:160 ( $\log_{10}X=2.2$ ). The standard deviation is about 4 ( $\log_{10}X=0.6$ ), the sample size is calculated:

Hypothesis 1, one-sided 2.5% significance level, 90% study power, GMT ratio of group A/group B Non-inferiority Margin is 0.67 ( $\log_{10}X = -0.174$ ), the ratio of group A and group B is 1:1, and the sample size is 35 per group.

Hypothesis 2, one-sided 2.5% significance level, and the ratio of group A and group B is 1:1. To ensure at least an 90% study power, a sample size of 86 per group could show that the GMT level of group A after immunization is better than that of group B.

Therefore, in order to meet both assumptions and considering a drop off of 10%, the sample size of about 100 people per group. Considering the difficulty of recruiting, Group C and Group D will have 50 persons in each to explore for exploratory purpose. The total sample size is about 300.

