## 4. Clinical Trial Endpoint

### 4.1 Primary Endpoint

- (1) The incidence of adverse reactions in each group within 28 days after the booster vaccination;
- (2) Neutralising antibodies to live SARS-CoV-2 (GMT) at 14 days after the booster vaccination.

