#### **4.2.2 Humoral immunogenicity endpoints**

The following exploratory endpoints were defined for emergency and routine immunization schedules, respectively:

- (1) GMTs of anti-SARS-CoV-2 S and N protein specific antibody (ELISA) at day 14, day 28 and month 6 after the booster vaccination in each group;
- (2) GMTs of neutralizing antibodies to live SARS-CoV-2 at day 28 and month 6 after the booster vaccination in each group;
- (3) The Geometric Mean of the Fold Increase (GMFI) of antibody level of anti-SARS-CoV-2 S and N protein specific antibody (ELISA) at day 14, day 28 and month 6 compared with day 0 after the booster vaccination in each group;
- (4) The Geometric Mean of the Fold Increase (GMFI) of neutralizing antibodies to live SARS-CoV-2 at Day 14, Day 28 and month 6 compare with day 0 after the booster vaccination in each group;
- (5) Proportion of the participants with at least a four-fold increase of the binding antibodies against SARS-CoV-2 S and N protein at day 14, day 28 and month 6 after the booster vaccination ( $\geq 4$  times increased);
- (6) Proportion of the participants with at least a four-fold increase of neutralizing antibodies against live SARS-CoV-2 virus, as compared to baseline, at day 14, day 28 and month 6 after the booster vaccination ( $\geq 4$  times increased);

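### The primary neutralising-antibody endpoint is at Day 14, but the hypotheses behind 86 per group and 90% power are set at Day 28, a secondary time point, with no assay named

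*Combined protocol and SAP*

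**What the plan says.** **Primary endpoint.** Protocol 3.1.1 gives "Neutralising antibodies to live SARS-CoV-2 (GMT) at after the boost vaccination 14 days", and SAP 4.1 gives "Neutralising antibodies to live SARS-CoV-2 (GMT) at 14 days after the booster vaccination". The synopsis agrees.

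**Secondary endpoint.** Protocol 3.1.2.2 lists "GMT of neutralising antibodies to live SARS-CoV-2 at Day28 and Month 6 after the boost vaccination in each group", and SAP 4.2.2 lists "GMTs of neutralizing antibodies to live SARS-CoV-2 at day 28 and month 6 after the booster vaccination in each group". The synopsis agrees again. The S and N protein ELISA GMTs at Day 28 are also secondary.

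**Hypotheses.** Protocol 3.2 states Hypothesis 1 as "GMT of Group A is not inferior to that in the group B at Day28 after the boost vaccination" and Hypothesis 2 as "GMT of Group A is superior to that in the group B at Day28 after the boost vaccination". SAP 3.3 says the same ("GMT of Group A is superior to that in the group B at Day 28 after the boost vaccination"), as does the synopsis. The protocol orders the two tests: "If Hypothesis 1 is valid, further statistical inference is made for Hypothesis 2".

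**Sizing.** The planning values are GMTs of 1:80 after the inactivated booster and 1:160 after the Ad5 booster, a log10 SD of 0.6, one-sided 2.5% and 90% power. Hypothesis 2 gives 86 per group. Hypothesis 1, with a GMT-ratio margin of 0.67, gives 35. The margin and the 35 appear in the synopsis and SAP 3.3 but not in protocol 3.2. The sentences giving the GMTs and SD name no day; only the hypotheses do.

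**Analysis.** SAP 6.4 compares GMTs between groups by t test at Day 14 and at the later visits alike. SAP 6.7 calls the study exploratory and makes no multiplicity adjustment.

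**The concern.** The primary endpoint and the powered hypotheses should describe the same comparison, and here they differ by two weeks. The same pairing recurs in the synopsis, the protocol body and the SAP, so it is not a single slip, and no section explains or reconciles it. Because the hypotheses name no assay, they could refer to neutralising or ELISA titres. Every Day 28 GMT is secondary, so the powered test falls on a secondary endpoint on any reading.

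At stake is which result is the trial's primary immunogenicity conclusion. If the two days disagree, for instance superiority at one and not at the other, the plan does not say which decides. Protocol 3.4.3 and 6.2.3 (SAP 3.2.3 and 6.10) place the initial analysis and unblinding after the Day 28 data are in, so both days' results would be available together. The 90% power figure could also be read as belonging to the declared primary endpoint, which the documents do not establish.

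**Working it through.** **1. Reproduce the plan's sizes.** Inputs from protocol 3.2 and SAP 3.3: log10 difference 2.2 − 1.9 = 0.3; SD 0.6; one-sided 2.5%; 90% power; 1:1 allocation.

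*Superiority.* Normal approximation: n = 2(1.960 + 1.282)² × 0.6² / 0.3² ≈ 84.1, so 85 per group. With the exact two-sample t test, noncentrality is 0.3 / (0.6 × √(2/n)):

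- n = 85 gives 89.99%
- n = 86 gives 90.3%

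The stated 86 is reproduced.

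*Non-inferiority.* The distance from the margin is 0.3 + 0.174 = 0.474. Normal approximation: 2(3.242)² × 0.36 / 0.474² ≈ 33.7, so 34. The exact t test needs 35 (90.3%). The stated 35 is reproduced.

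*Dropout.* 86 / 0.90 = 95.6, so 96, which the plan rounds to about 100.

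The arithmetic is sound. The open question is which endpoint it describes.

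**2. Set the roles side by side.**

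| | Day 14 | Day 28 |
|---|---|---|
| Neutralising GMT listed as | Primary | Secondary |
| Between-group t test (SAP 6.4) | Yes | Yes |
| Hypotheses 1 and 2 | None stated | Both, assay unnamed |
| Margin, effect size and power tied to this day | None | Only through the hypotheses |

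**3. Power at Day 14 under assumed values.** The documents give no Day 14 planning values, so the ratios below are assumptions. With 100 per group and 10% dropout, 90 are evaluable. Exact t power at SD 0.6, one-sided 2.5%:

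| Assumed Day 14 GMT ratio | log10 difference | Power |
|---|---|---|
| 2.0 | 0.301 | 92% |
| 1.75 | 0.243 | 77% |
| 1.5 | 0.176 | 50% |

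At ratio 2 with an assumed SD of 0.7, power is 82%. If ratio 2 and SD 0.6 hold at Day 14, the required size stays at 86.

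**4. Error rate if either day could carry the claim.** Take two one-sided 2.5% tests under a bivariate normal null. The chance that at least one succeeds is 1 − P(Z₁ ≤ 1.96, Z₂ ≤ 1.96). The correlation between the Day 14 and Day 28 comparisons is assumed:

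| Correlation | False-positive rate |
|---|---|
| 0.5 | 4.5% |
| 0.7 | 4.2% |
| 0.8 | 3.9% |
| 0.9 | 3.5% |

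**The case against.** The best reply is that SAP 6.7 calls the trial exploratory, that SAP 6.4 does plan a Day 14 comparison of neutralising GMT, and that no section allows success on whichever day looks better. Much of this stands, and it limits what can be said.

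- A reader might infer that Day 14 is untested. It is not: a t test is planned, with the two-sided 0.05 threshold of SAP 6.1. What is missing is a stated hypothesis, margin, effect size and power.
- A reader might infer that Day 14 is underpowered. The documents do not show this. The GMT and SD sentences name no day, and if those values hold at Day 14 the size is unchanged.
- A reader might infer that the plan runs at 3.5% to 4.5% instead of 2.5%. That needs an either-day rule, which the plan does not contain. It does not exclude one either, and SAP 6.7 waives adjustment, so the figure describes a possible use of the plan.

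The exploratory label does not remove the mismatch. The plan still sets ordered hypotheses with a margin, an alpha and a power, and sizes Groups A and B on them. The documents disagree about how formal the A-versus-B comparison is, and the label does not say which day decides it.

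**Conclusion.** The inconsistency is real and unreconciled. The declared primary immunogenicity endpoint is Day 14 live-virus neutralising GMT, while the hypotheses that produce 86 per group and 90% power are at Day 28, with the assay unstated. The stated power therefore cannot be cited for the declared primary endpoint as the documents stand. This is a fault of specification, not of calculation.

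Its numerical consequences are conditional. Power at Day 14 is 92% with 90 evaluable per group if the GMT ratio is 2 and the SD 0.6, and falls to about 77% or 50% at assumed ratios of 1.75 or 1.5. The false-positive rate reaches about 3.5% to 4.5% only if either day may carry the claim, at assumed correlations of 0.9 to 0.5. The correction should be made before unblinding, because it settles which result is the primary one.

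**What to change.** Before any unblinded data are seen, name one assay (live-virus neutralising GMT) and one day for both the primary immunogenicity endpoint and Hypotheses 1 and 2. Make the change in the synopsis, protocol 3.1.1 and 3.2, and SAP 3.3 and 4.1, and list the other day as secondary. Two routes are consistent with the documents:

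- **Move the hypotheses to Day 14.** The primary endpoint stays as declared. Keep the 90% power statement only if the sponsor confirms a GMT ratio of 2 and SD 0.6 for Day 14; otherwise restate the power. Relabelling the existing values without support is not enough.
- **Make Day 28 neutralising GMT primary.** The sample-size statement then stands, with the assay added. Day 14 moves to the secondary list, so protocol 3.1.2.2 and SAP 4.2.2 change too.

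The cost is a wording amendment. Both blood draws are already scheduled, so no visits or samples are added. The downside is that the day not chosen can no longer carry the primary claim, and under the first route the stated power may become less favourable.

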##### **3.1.2 Secondary endpoints**

###### **3.1.2.1 Safety endpoints**

- Incidence of solicited adverse reactions at 0-14 days after the boost vaccination;
- Incidence of unsolicited adverse reactions at 0-28 days after the boost vaccination;
- Incidence of serious adverse events (SAE) at 6 months after the boost vaccination;

###### **3.1.2.2 Humoral immunogenicity endpoints**

- GMT of anti-SARS-CoV-2 S and N protein specific antibody (ELISA) at Day14, Day28 and Month 6 after the boost vaccination in each group;
- GMT of neutralising antibodies to live SARS-CoV-2 at Day28 and Month 6 after the boost vaccination in each group;
- The Geometric Mean of the Fold Increase (GMFI) of antibody level of

anti-SARS-CoV-2 S and N protein specific antibody (ELISA) at Day14, Day28 and Month 6 compare with Day0 after the boost vaccination in each group;

- The Geometric Mean of the Fold Increase (GMFI) of neutralising antibodies to live SARS-CoV-2 at Day14, Day28 and Month 6 compare with Day0 after the boost vaccination in each group;
- Proportion of the participants with at least a four-fold increase of the binding antibodies against SARS-CoV-2 S and N protein at Day 14, Day 28 and Month 6 after the boost vaccination ( $\geq 4$  times increased);
- Proportion of the participants with at least a four-fold increase of neutralizing antibodies against live SARS-CoV-2 virus, as compared to baseline, at Day 14, Day 28 and Month 6 after the boost vaccination ( $\geq 4$  times increased);

### **3.1.2.3 Endpoint of cellular immunity study**

- The levels of IFN- $\gamma$ , TNF- $\alpha$ , IL-5, IL-4, IL-13, and Th1/Th2 cytokine secreted by specific T cells in each group at the Day14 after the boost vaccination;

### **3.1.3 Exploratory endpoints**

- Isotypes of binding antibodies IgG against SARS-CoV-2 S protein at Day 14, Day 28 and Month 6 after the boost vaccination;
- Cross neutralizing of the antibodies to variants of SARS-CoV-2 at Day 28 after the boost vaccination;
- The differentiation of immune cell and antibody spectrum of B cells, T cells and other major immune cell in each group at Day14, Day 28 and Month 6 after the boost vaccination.

## **3.2 Sample size**

(1) Hypothesis 1: GMT of Group A is not inferior to that in the group B at Day28 after the boost vaccination.

(2) Hypothesis 2: GMT of Group A is superior to that in the group B at Day28 after the boost vaccination.

Three to six months after two doses of inactivated vaccine, the baseline GMT level before the booster is expected to be about 1:40 ( $\log_{10}X=1.6$ ), and 1:80 ( $\log_{10}X=1.9$ ) after one dose of inactivated vaccine. After receiving one dose of the

recombinant COVID-19 vaccine (Ad5 vector) as booster, the GMT is estimated to reach 1:160 ( $\log_{10}X=2.2$ ). The standard deviation is about 4 ( $\log_{10}X=0.6$ ), the sample size is calculated:

At one-sided 2.5% significance level, and the ratio of group A and group B is 1:1. To ensure at least an 90% study power, a sample size of 86 per group could show that the GMT level of group A after immunization is better than that of group B. Therefore, in order to meet both assumptions and considering a drop off of 10%, the sample size of about 100 people per group. Considering the difficulty of recruiting, Group C and Group D will have 50 persons in each to explore for exploratory purpose. The total sample size is about 300.

Table 1. Sample size of each study group

| group   | sample size | Prime immunization                    | Boost immunization                                 | Immunization procedure                                                                                              |
|---------|-------------|---------------------------------------|----------------------------------------------------|---------------------------------------------------------------------------------------------------------------------|
| Group A | 100         | Inactivated COVID-19 vaccine (2 dose) | Recombinant COVID-19 vaccine (Ad5 vector) (1 dose) | Three to six months after the second vaccination of inactivated vaccine, boost immunization will be administrated.  |
| Group B | 100         |                                       | Inactivated COVID-19 vaccine (1 dose)              |                                                                                                                     |
| Group C | 50          | Inactivated COVID-19 vaccine (1 dose) | Recombinant COVID-19 vaccine (Ad5 vector) (1 dose) | One to two months after the first vaccination of inactivated vaccine, the boost immunization will be administrated. |
| Group D | 50          |                                       | Inactivated COVID-19 vaccine (1 dose)              |                                                                                                                     |
|         | 300         |                                       |                                                    |                                                                                                                     |

\*If Hypothesis 1 is valid, further statistical inference is made for Hypothesis 2. The GMT comparison of group C and group D after immunization is taken as the preliminary exploration, and no statistical inference is made for the sample size estimation. Considering the difficulty of recruiting people of groups C and D, the sample size is set to half of groups A and B.

### 3.3 Research Plan

A total of 4 visits, at day 0 (before vaccination), and at day14, day28 and 6 months after the boost vaccination

Figure2. Program and contents of visit plan of regimen subjects

| Visit No.                                          | V1      | V2      | V3      | V4      |
|----------------------------------------------------|---------|---------|---------|---------|
| Visit interval                                     | 第 0 天   | V0+14 天 | V0+28 天 | V0+6 个月 |
| Time window                                        | (±3 天)  | (+3 天)  | (+4 天)  | (±15 天) |
| Informed consent                                   | ●       |         |         |         |
| Demographic information collection                 | ●       |         |         |         |
| Physical examination and preliminary screening     | ●       |         |         |         |
| Randomization                                      | ●       |         |         |         |
| Blood collection                                   | ●(20ml) | ●(20ml) | ●(20ml) | ●(20ml) |
| Observation for 30 min post-vaccination            | ●       |         |         |         |
| Safety visit(AR/AE)                                | ●       | ●       | ●       |         |
| Report serious adverse event(SAE)※                 | ●       | ●       | ●       | ●       |
| Distribution of diary card                         | ●       |         |         |         |
| Return of diary card and distribute a contact card |         | ●       |         |         |
| Return of contact card                             |         |         | ●       |         |
| Record on the Vaccination and Visit Record Form    | ●       | ●       | ●       | ●       |
| Record the combination drug/vaccine                | ●       | ●       | ●       | ●       |

